#### Surveys

Face-to-face interviews at baseline will collect data on socio-demographic characteristics, obstetric history, oral care behaviors, OHRQoL, and lifestyle. An endline survey, conducted post-delivery before hospital discharge, will obtain data on oral health care behaviors, OHRQoL, and lifestyle.

A structured questionnaire was developed in English, translated into Bengali, and then back-translated into English. The accuracy of the translation and reliability of the contents were reviewed by two native Bengali speakers with expertise in MNCH and dentistry. A pre-test was conducted to identify any biases or ambiguities and to assess whether the questions are culturally appropriate.

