#### Antenatal records

Data on birth outcomes, including gestational age at delivery and birth weight, will be extracted from antenatal records. Additional information will also be collected, including maternal height, pre-pregnancy body mass index, blood glucose level, pregnancy complications, and the number of antenatal checkups attended.

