### Statistical analyses

The primary analysis will follow the intention-to-treat principle, whereby participants will be analyzed according to their assigned groups, regardless of adherence to CHG mouthwash use during pregnancy. Missing data will be handled using multiple imputation procedures available in the MI suite of Stata. To assess the robustness of the findings, sensitivity analyses will be conducted by comparing results from imputed and non-imputed datasets.

Data from the baseline and endline surveys, dental checkups, and antenatal records will be compared across groups to evaluate the effects of the intervention (SRP combined with CHG mouthwash use) on the primary (PTB) and secondary outcomes (LBW, periodontal disease, and OHRQoL). Initial analyses will include descriptive statistics for participants’ socio-demographic and other basic characteristics, followed by bivariate analyses to examine differences in baseline variables between groups A and B, and between groups B and C.

To estimate the causal effect of the intervention on birth outcomes, comparisons will be made between groups A and B. To investigate whether previously reported associations between periodontal disease and adverse birth outcomes hold in our population, groups B and C will be compared.

For multivariable analyses, two types of regression models will be employed. (1) Multiple regression models will be used to evaluate outcomes measured only at endline. (2) Mixed-effect regression models will be applied for outcomes assessed at both baseline and endline, accounting for potential intra-individual serial correlations in the residual.

Specifically, to assess the effectiveness of the intervention on birth outcomes (PTB and LBW), a multiple regression model will be used, with intervention status (group A or B) as the main predictor, adjusting for potential covariates (socio-demographic characteristics, lifestyle, pregnancy-related characteristics, and pregnancy outcomes). For oral health outcomes (periodontal disease and OHRQoL), mixed-effects regression models will be used, including intervention status (group A or B), time point (baseline or endline), and their interaction terms, while adjusting for potential covariates.

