To evaluate the association between baseline periodontal disease and birth outcomes in groups B and C, a multiple regression model will be employed, with baseline periodontal status (group B or C) as the exposure, adjusting for potential confounders (socio-demographic characteristics and lifestyle at baseline). To assess change in periodontal status between baseline and endline in groups B and C, another multiple regression model will be used with similar covariate adjustments.

To evaluate the association of baseline periodontal diseases and OHRQoL in groups B and C, mixed-effect regression models will be fitted, including baseline periodontal status (group B or C), time point (baseline or endline), and their interaction term, adjusting for the possible confounding factors listed above.

Statistical significance will be set at a *p*-value of < 0.05. All statistical analyses will be conducted using IBM SPSS Statistics version 26.0 (IBM Corp, Armonk, NY, USA) or Stata version 16.0 (StataCorp LLC, College Station, TX, USA).

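### The A-versus-B model for preterm birth and low birth weight adjusts for pregnancy outcomes and does not limit its other covariates to baseline

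*Protocol article*

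**What the plan says.** All of the following is from the protocol article.

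- **Aim (Statistical analyses).** "To estimate the causal effect of the intervention on birth outcomes, comparisons will be made between groups A and B". The governing principle is intention to treat: "The primary analysis will follow the intention-to-treat principle, whereby participants will be analyzed according to their assigned groups".
- **Model (Statistical analyses).** "to assess the effectiveness of the intervention on birth outcomes (PTB and LBW), a multiple regression model will be used", with group A or B as the main predictor, "adjusting for potential covariates (socio-demographic characteristics, lifestyle, pregnancy-related characteristics, and pregnancy outcomes". The sentence places no time limit on any of the four covariate domains.
- **Observational comparison of B and C (same section).** The birth-outcome model there is described as "adjusting for potential confounders (socio-demographic characteristics and lifestyle at baseline". It is tied to baseline and does not include pregnancy outcomes.
- **When the data arise.** Lifestyle is recorded at baseline and again after delivery (Surveys): "An endline survey, conducted post-delivery before hospital discharge, will obtain data on oral health care behaviors, OHRQoL, and lifestyle". Under Antenatal records, "Data on birth outcomes, including gestational age at delivery and birth weight, will be extracted from antenatal records", and the additional items include "pregnancy complications, and the number of antenatal checkups attended". The same list also holds maternal height and pre-pregnancy body mass index, which precede randomisation.
- **Vocabulary for earlier pregnancies.** Surveys calls this obstetric history; Socio-demographic data calls it birth history.

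**The concern.** Randomisation makes A and B comparable on everything that precedes allocation. Adjusting for pre-randomisation variables keeps that protection; adjusting for what happens afterwards can lose it. Such a variable may lie on the causal path (prematurity on the way to LBW), may follow from the endpoint (birth weight when the endpoint is PTB), or may define the endpoint (gestational age at delivery). In the first case the model removes part of the effect the trial was set up to measure. In the second it costs precision and may also shift the estimate. In the third it cannot be fitted.

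The model concerned covers the primary outcome, and the article describes no unadjusted effect estimate on birth outcomes beside it. The open timing of the other two domains adds a second risk: endline lifestyle, complications or number of checkups could be brought in after the outcomes are known.

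**Working it through.** **1. The passages side by side.** The A-versus-B covariate list names pregnancy outcomes and gives no timing. The B-versus-C list says baseline and omits pregnancy outcomes. So the randomised comparison, where adjustment is least needed, has the looser rule.

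**2. The plan's own figures (Sample size calculation).** Inputs: PTB 16.2% versus 4.7%, 80% power, 5% significance (two-sided assumed), 20% attrition.
- Two proportions, pooled variance: n = [1.96·√(2·0.1045·0.8955) + 0.842·√(0.162·0.838 + 0.047·0.953)]² / 0.115² ≈ 110 per group.
- With continuity correction: 127, against the stated 128. The figure reproduces to within one.
- 128 / 0.80 = 160 per group, as stated.

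**3. Effect without post-randomisation covariates.**
- Odds ratio (OR) = (0.047/0.953) / (0.162/0.838) = 0.255, so ln OR = −1.366.
- Expected cells at 128 per arm: 20.7 and 107.3 in B, 6.0 and 122.0 in A. SE = √(1/20.7 + 1/107.3 + 1/6.0 + 1/122.0) ≈ 0.48.
- Wald power = Φ(1.366/0.482 − 1.96) ≈ 81%. The pooled z test without continuity correction gives 85.7%.

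**4. LBW model adjusted for PTB.** Assumption: treatment affects LBW only through prematurity. LBW risk in an arm = P(PTB)·P(LBW|preterm) + P(term)·P(LBW|term). The two conditional risks are assumed.

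| P(LBW given preterm) | P(LBW given term) | LBW in B | LBW in A | OR, unadjusted | OR, adjusted for PTB |
|---|---|---|---|---|---|
| 0.60 | 0.15 | 22.3% | 17.1% | 0.72 | 1.00 |
| 0.70 | 0.12 | 21.4% | 14.7% | 0.63 | 1.00 |
| 0.80 | 0.10 | 21.3% | 13.3% | 0.57 | 1.00 |

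First row, for example: 0.162·0.60 + 0.838·0.15 = 0.223, and 0.047·0.60 + 0.953·0.15 = 0.171. Within each PTB stratum the arms have the same LBW risk, so the adjusted OR is 1.00 by construction.

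**5. PTB model adjusted for LBW or birth weight**, 128 per arm.
- LBW depends only on PTB status (the three settings above): the OR stays at 0.255, and Wald power falls from 81% to 77%, 73% and 68%.
- Gestational age is shifted to give 16.2% versus 4.7% (SD 1.8 weeks), birth weight rises 180 g per week with residual SD 350 g, and continuous birth weight is the covariate: by simulation the OR moves from 0.25 to 0.38, and power falls from about 85–87% to 41%.
- Same model with residual SD 450 g: OR 0.34, power about 52%. Binary LBW in place of birth weight: OR about 0.28–0.31, power about 63–75%.

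The simulated figures carry Monte Carlo error of a few points.

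**6. PTB model adjusted for gestational age at delivery.** PTB is delivery before 37 weeks, so this covariate determines the outcome. There is complete separation and no treatment effect can be estimated.

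**The case against.** The strongest reply has four parts.

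- **Loose wording.** Pregnancy outcomes may have been meant as outcomes of earlier pregnancies; the section calls the trial endpoints birth outcomes, and the B-versus-C model shows that the authors know what a baseline restriction is. This does not carry the point. Earlier pregnancies have their own names elsewhere in the article, and nothing here says that they are meant.
- **Unseen analysis plan.** A list of potential covariates by domain fixes no variables, and a statistical analysis plan could refine it. That is true of the final list. But the article itself names a class of covariate that does not belong in this model, so this is a statement to correct and not an omission.
- **Reach.** A reader might infer that lifestyle and pregnancy-related characteristics are post-randomisation as well. The article does not say so. It leaves their timing open, and the records that hold complications and checkups also hold height and pre-pregnancy body mass index. This part of the reply stands. Nor does the article name the adjusted model as the only primary estimate, though it describes no unadjusted effect estimate.
- **Size.** A reader might infer that the trial loses most of its power. That holds only under some assumed inputs; under others the PTB odds ratio does not move and the power loss is modest. A reader might also infer sparse-data bias from an overlong model, but the article gives no covariate count, so that cannot be shown. This part stands too.

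**Conclusion.** The covariate rule is wrong as written. Outcomes of the current pregnancy cannot be adjusted for in the model that is to give the causal, intention-to-treat effect of A versus B on PTB and LBW. For the lifestyle and pregnancy-related domains the fault is narrower: the text does not restrict them to baseline, although later measurements of both kinds are collected.

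The size is a range, not a single figure. At one end, LBW purely downstream of PTB leaves the PTB odds ratio unchanged and takes power from 81% to no lower than 68%. At the other, a prematurity-mediated LBW effect vanishes altogether, or the PTB model cannot be fitted. Continuous birth weight with a steep slope lies between, at an odds ratio of 0.38 and 41% power. Only the PTB rates and the group size come from the article. The conditional LBW risks, the birth-weight slope and SDs, and the choice of variable that enters are assumptions.

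**What to change.** In Statistical analyses, delete pregnancy outcomes from the covariates of the A-versus-B birth-outcome model. State that its covariates are prespecified and measured before randomisation, for example site (randomisation is blocked at each site), baseline socio-demographic characteristics, baseline lifestyle and obstetric history. Label any model that includes complications, number of checkups, endline lifestyle or another birth outcome as exploratory, and do not present it as the effect of the intervention. How many baseline covariates to use is for the trial team; this point sets no cap.

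The cost is wording only. No data, procedure or participant burden changes, and 128 evaluable and 160 enrolled per group stand. Trial status expects data collection to end in September 2026; the change should be dated and made before outcomes are analysed by group.

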#### Hypothesis

We hypothesize that integrating an intervention targeting periodontal disease—comprising SRP and CHG mouthwash use—into the MNCH CoC will reduce PTB and LBW, decrease the prevalence of periodontal disease, and improve OHRQoL.

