### Randomization and blinding

The trial includes three groups: group A (intervention) and groups B and C (control). All participants will first complete a face-to-face interview at the obstetrics and gynecology department following consent. They will then undergo a baseline dental checkup. Participants diagnosed with periodontal disease will be randomized to group A or B using blocked randomization via computer-generated sequence at each site. Those without periodontal disease will be assigned to group C.

Blinding will be maintained for the interviewers and data recorders, who will not be informed of group allocation. However, blinding will not be feasible for the dentists conducting dental checkups or for participants due to the nature of the intervention.

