##### Diagnosis of periodontal disease

BOP, PPD, and CAL will be measured at six points on each tooth and used to diagnose periodontal diseases, including gingivitis and periodontitis. Gingivitis is diagnosed when BOP is present at 10% or more of the total number of periodontal sites examined. Periodontitis will be diagnosed if either of the following criteria is met: (1) interdental CAL is observed at ≥ 2 non-adjacent teeth, or (2) a buccal or palatal/lingual site exhibits a CAL of ≥ 3 mm and PPD of ≥ 4 mm at ≥ 2 teeth [45, 46].

Participants diagnosed with periodontal disease will be randomized into either the intervention group A or control group B. Participants without periodontal disease will be allocated to control group C.

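### With periodontal disease present in all of A and B at baseline, the group-by-time interaction planned for that diagnosis cannot be estimated on the logit scale; an endline comparison can

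*Protocol article*

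**What the plan says.** Entry to the two randomized arms depends on the baseline diagnosis. Randomization and blinding states: "Participants diagnosed with periodontal disease will be randomized to group A or B using blocked randomization via computer-generated sequence at each site". Diagnosis of periodontal disease repeats the rule: "Participants diagnosed with periodontal disease will be randomized into either the intervention group A or control group B". Women without the disease form group C.

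The diagnosis is set by thresholds, for example: "Gingivitis is diagnosed when BOP is present at 10% or more of the total number of periodontal sites examined". The Hypothesis expects the intervention to "decrease the prevalence of periodontal disease, and improve OHRQoL", which is the language of a yes/no outcome.

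Statistical analyses sorts outcomes by when they are measured: "Mixed-effect regression models will be applied for outcomes assessed at both baseline and endline". For A versus B it then specifies: "For oral health outcomes (periodontal disease and OHRQoL), mixed-effects regression models will be used, including intervention status (group A or B), time point", continuing with "time point (baseline or endline), and their interaction terms, while adjusting for potential covariates". No link function or distribution is named.

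For B versus C the article uses a different model for the same outcome: "To assess change in periodontal status between baseline and endline in groups B and C, another multiple regression model will be used".

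**The concern.** A group-by-time interaction measures how much more one arm changes from baseline than the other. That needs a baseline which can be expressed on the model's scale. Here everyone in A and B has the disease at baseline, so the baseline log-odds are infinite in both arms and the interaction is a difference of two infinite quantities.

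Periodontal disease is part of the stated hypothesis. It is also the outcome that shows whether the treatment improved the mouth at all, which a reader will want to know if the preterm-birth result is null. An analyst who follows the text with a logistic mixed model gets an interaction with no usable estimate or test, and must then choose a replacement after seeing the data.

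The B-versus-C change model raises a lesser question. B starts with the disease and C without it, so what does a difference in change mean?

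**Working it through.** **Inputs.** Baseline prevalence is 100% in A and in B, from the entry rule. The number per arm is 128, from Sample size calculation. The article gives no endline prevalence, so two pairs are assumed: A 40% / B 80% and A 50% / B 90%. In whole women the first pair is 51/128 and 102/128.

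**The plan's own figure.** The 128 is for preterm birth (16.2% versus 4.7%, 80% power, 5%). The two-sided pooled formula gives [1.960·√(2 × 0.1045 × 0.8955) + 0.842·√(0.162 × 0.838 + 0.047 × 0.953)]² / 0.115² = 110. With the continuity correction it gives 127, against 128 stated, and 128/0.80 = 160. The figure is reproduced to within one woman. It serves here only as the number per arm; the article gives no figure for periodontal disease.

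**Logit link, algebra.** Write logit P = a + bG + cT + dGT, with G = 1 for A and T = 1 at endline.
- All baseline outcomes are 1, so the likelihood keeps rising as a and a + b go to infinity.
- Now set d = 0. Let a → ∞ and c → −∞ with a + c held at B's endline logit, and let b equal the endline log odds ratio. Baseline is fitted perfectly and both endline rates are matched exactly.
- The model without the interaction therefore reaches the same maximum likelihood as the model with it. The likelihood-ratio statistic for d is 0 for any endline rates strictly between 0 and 1. Covariates do not help, because the baseline outcome is still constant.

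**Logit link, numbers.**
- *Random-intercept logistic model by quadrature.* The group main effect was fixed at −5, 0 or +5 and the random-intercept SD at 0, 1, 2 or 4. Every combination gives the same maximized log-likelihood. For 40%/80% the interaction runs from +3.2 to −9.8; for 50%/90% from +2.8 to −10.6.
- *Conditional endline log odds ratio.* For 40%/80% it is −1.78, −2.12, −2.88 and −4.76 at SD 0, 1, 2 and 4, all at equal likelihood, so the variance is not identified either. Forcing the interaction to zero in this case gives a likelihood-ratio statistic of 0 to rounding at each SD.
- *Ordinary logistic model with the interaction (40%/80%).* After 5, 10, 20 and 30 iterations the intercept is 6.6, 11.6, 21.6 and 31.6. The standard error of the interaction goes from 2.0 to 542,614.
- *Simulation, ordinary logistic, 50 trials per scenario.* At assumed endline rates of 50% or 30% (A) versus 90% (B), and at 90% in both, the interaction statistic never exceeded 1.5 × 10⁻⁸. An endline-only test on the same data rejected in 100%, 100% and 6%.

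**Endline only, 40%/80%.** Log odds ratio = ln(51/77) − ln(102/26) = −0.412 − 1.367 = −1.78. SE = √(1/51 + 1/77 + 1/102 + 1/26) = 0.28. Risk difference = 51/128 − 102/128 = −0.398.

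**Identity link, 40%/80%.** A linear mixed model on the 0/1 diagnosis gives an interaction of −0.398 (SE 0.056), equal to the endline risk difference. The random-intercept variance is estimated as 0. The SE agrees with √{[0.398 × 0.602 + 0.797 × 0.203]/128} = 0.056.

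**B versus C.** Let p_B and p_C be endline prevalences. Mean change is p_B − 1 in B (never above 0) and p_C − 0 in C (never below 0). The difference in change is p_B − p_C − 1, which is the endline difference shifted by a constant that comes from the group definitions. It cannot be positive.

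**The case against.** The strongest reply is that the article never says logit. Its one description of the mixed models speaks of serial correlation in the residual, which is the language of linear mixed models, and the link is something an article may leave to the analysis plan. On an identity link the planned interaction works. Over 20,000 simulated trials per scenario with 128 per arm and assumed rates, it rejected in about 5% under no effect (5.0% to 5.4%) and in 100% at 50% versus 90%. This stands, and the finding must be conditional on the link.

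The outcome's form is also not fully fixed. The Abstract speaks of the mother's periodontal status, gingivitis and periodontitis are separated, and BOP, PPD and CAL are recorded at both visits. A graded or continuous measure could vary at baseline, and the problem would not arise. This stands too, although no such measure is named as the modelled outcome and the Hypothesis speaks of prevalence.

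Three stronger readings are tempting, and the document supports none of them:
- *That the treatment effect itself is unidentifiable.* Only the logit-scale interaction and the random-intercept variance are. The randomized endline contrast is in the data and can be estimated.
- *That the planned test lacks power under any reading.* The identity-link result contradicts this.
- *That the B-versus-C model is unidentifiable in the same way.* It is a regression on change and can be fitted. The limit is on interpretation, in a comparison that is observational in any case. Regression to the mean around the 10% bleeding threshold may add to it, but nothing in the article allows its size to be stated.

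What the reply does not remove is that the article states a model for an outcome it describes as a diagnosis, and under the usual choice for such an outcome the model gives no usable result. Even where the model works, the constant baseline adds nothing to an endline comparison.

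**Conclusion.** The concern holds in conditional form and should be fixed. If periodontal disease is analysed as a yes/no diagnosis with a logit link, the group-by-time interaction and the random-intercept variance are not identifiable and a likelihood-ratio test of the interaction has no power. This follows from the entry rule and does not depend on the assumed endline rates; those rates affect only the illustrative numbers. The A-versus-B endline contrast stays estimable, and on an identity link the interaction reduces to the endline risk difference.

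For B versus C, the change model is estimable, but change in diagnosis can only be downward or zero in B and upward or zero in C, so the difference in change should not be interpreted.

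One secondary outcome is affected. Preterm birth, low birth weight, OHRQoL and the sample size are untouched.

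**What to change.** - **A versus B.** State the form of the outcome and the link. Compare periodontal disease at endline only, by logistic or log-binomial regression or a risk difference. Adjust for site, since randomization is done at each site, and for baseline severity (percent of sites with BOP, PPD, CAL). Alternatively, model a continuous periodontal measure at endline adjusted for its baseline value.
- **OHRQoL.** Keep the mixed model. Its baseline is not fixed by the entry rule.
- **B versus C.** Replace the comparison of change in diagnosis with persistence in B and incidence in C, reported separately.

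The cost is analysis wording only. BOP, PPD and CAL are already measured at six points per tooth, with checkups at baseline and endline, and no change to design, data collection or sample size follows. The wording should be settled before outcome data are examined by group.

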### Data collection and study outcomes

The primary outcome is PTB (< 37 weeks gestation). Secondary outcomes include LBW (< 2500 g), periodontal disease, and OHRQoL.

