##### Oral health

Data on oral hygiene practices, especially tools, timing, and frequency of oral care, and knowledge of the epidemiology and prevention of periodontal disease will be collected. OHRQoL will be assessed via the Oral Health Impacts Profile (OHIP-14) [38, 39]. The profile consists of 14 questions in seven domains: functional limitation, physical pain, psychological discomfort, physical disability, psychological disability, social disability, and handicap. Responses are recorded, using a five-point Likert scale to record the responses: never = 1, hardly ever = 2, occasionally = 3, fairly often = 4, and very often = 5. The total score will be dichotomized into high versus low impact, using a median split.

The presence of periodontal disease symptoms will be assessed, using ten questions from a self-report check list developed by the Japanese Academy of Clinical Periodontology [40]. The questions include items related to bad breath, sticky mouth, bleeding during toothbrushing, swollen/drooping/bleeding gums, and problems with the teeth. The presence or absence of any symptoms will be included in further analysis.

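### The group-by-time model for OHRQoL in A versus B estimates a difference in change rather than a baseline-adjusted endline effect; it is valid but generally gives away precision

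*Protocol article*

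**What the plan says.** OHRQoL is a named secondary outcome (Data collection and study outcomes: "Secondary outcomes include LBW (< 2500 g), periodontal disease, and OHRQoL"). It is measured with the OHIP-14 at baseline and after delivery. Under Oral health, the score is made binary: "The total score will be dichotomized into high versus low impact, using a median split".

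The Statistical analyses section sets a general rule, "Mixed-effect regression models will be applied for outcomes assessed at both baseline and endline", and then gives the form for A versus B: "mixed-effects regression models will be used, including intervention status (group A or B), time point (baseline or endline), and their interaction terms". The only other terms are unspecified covariates. Baseline OHRQoL is not named among them, and it already enters the model as an outcome row. No constraint that A and B share a baseline mean is stated.

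On timing, Randomization and blinding says "All participants will first complete a face-to-face interview at the obstetrics and gynecology department following consent". The dental checkup follows, and then "Participants diagnosed with periodontal disease will be randomized to group A or B using blocked randomization via computer-generated sequence at each site". The Surveys section confirms that the interview carries the outcome: "Face-to-face interviews at baseline will collect data on socio-demographic characteristics, obstetric history, oral care behaviors, OHRQoL, and lifestyle".

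The same group, time and interaction form is used for OHRQoL in B versus C, where the groups are defined by disease status and not by randomisation.

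**The concern.** In a randomised comparison with the outcome measured before allocation, any baseline difference between arms is chance. A model with a free group term estimates that difference and then, through the interaction, subtracts all of it from the endline difference. A baseline-adjusted analysis subtracts only the part that predicts the endline value. The full subtraction adds noise and removes no bias.

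At stake are the width of the interval and the power for OHRQoL, which is also part of the trial's stated hypothesis. The data needed for the more precise analysis are already being collected.

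**Working it through.** **Inputs from the protocol.** 128 analysable women per arm and a 5% significance level (Sample size calculation), taken as two-sided; OHIP-14 at two time points; median split; 1:1 target sizes.

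**Inputs not in the protocol, so assumed.** Baseline-to-endline correlation rho of 0.3, 0.5 and 0.7; the effect size; the ratio of endline to baseline SD.

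**The plan's own figure.** The 128 is for preterm birth, 16.2% against 4.7%, at 80% power. The usual two-proportion formula gives 110 per group uncorrected and 127 with continuity correction, which agrees with 128 to within rounding. 128 / 0.80 = 160. No power is stated for OHRQoL; 128 is used below only as the number analysed.

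**What the model estimates.** With two time points, complete data and free group, time and interaction terms, the interaction equals (endline mean minus baseline mean in A) minus the same in B. The model's endline contrast (group plus interaction) is the raw endline difference, so it is not baseline-adjusted either.

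**Continuous score, equal SDs.** In units of SD squared, the per-woman variance is:
- difference in change: 2(1 − rho)
- baseline-adjusted: 1 − rho²
- ratio, adjusted to planned: (1 + rho)/2

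Take the effect that the planned contrast detects with 80% power, d = 2.8016 × √(2 × 2(1 − rho)/128). Adjusted power is Φ(d / √(2(1 − rho²)/128) − 1.96).

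| rho | variance ratio | d (SD) | planned | adjusted |
|---|---|---|---|---|
| 0.3 | 0.65 | 0.414 | 80% | 93.5% |
| 0.5 | 0.75 | 0.350 | 80% | 89.9% |
| 0.7 | 0.85 | 0.271 | 80% | 86.0% |

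**Dependence on the anchor.** If instead the adjusted analysis has 80% power, the planned one has 61.7%, 67.9% and 73.3%. With fixed effects of 0.2 to 0.5 SD, the gap runs from 0.1 to 18.4 points.

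**Dependence on equal SDs.** Let s be endline SD divided by baseline SD. In units of baseline SD squared, the variances are 1 + s² − 2·rho·s (planned) and s²(1 − rho²) (adjusted). Their difference is (1 − rho·s)², which is never negative but is zero when s = 1/rho. At s = 1.3 and rho = 0.7 they are 0.870 and 0.862, almost equal. With the planned contrast at 80%, adjusted power at rho 0.3, 0.5 and 0.7 is:
- s = 1.3: 87.7%, 83.5%, 80.4%
- s = 1/1.3: about 98%, 97%, 96%

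**Median-split outcome, as the protocol plans it.** Simulation at 128 per arm: bivariate normal latent score with equal SDs, each visit cut at its own pooled median, latent shift of 0.45 SD at endline. The planned contrast is represented by a marginal difference in change of log-odds with a Wald test, as a stand-in for the mixed logistic interaction. The comparator is logistic regression of endline status on group and baseline status.

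| latent rho | difference in change | baseline-adjusted |
|---|---|---|
| 0.3 | about 62% | about 83% |
| 0.5 | about 69% | about 85% |
| 0.7 | about 81% | about 91% |

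With no shift, both tests reject in about 5% of trials (4.4% to 5.5%).

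**The case against.** The best defence is that group, time and interaction is a common and valid longitudinal model, that nothing in the protocol contradicts it, and that OHRQoL is a secondary outcome with no power claim. The article does not say which coefficient is the treatment effect, and final contrasts and covariate lists are often left to an analysis plan. Most of this stands, and it limits the point to efficiency. It does not remove the point: the model terms are fixed in the text, and neither the interaction nor the endline contrast from those terms is adjusted for baseline.

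A second objection is that any power figure depends on quantities the protocol does not give. That is correct. A reader might take the 6 to 14 points in the equal-SD table as a property of the design. The documents do not support that. Those figures need an assumed correlation, equal SDs, an effect at which the planned test has exactly 80% power, and a continuous score, whereas the protocol dichotomises the score. The binary figures in turn rest on a marginal stand-in and not on the mixed logistic model itself.

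A third objection concerns the remedy. For a continuous score, endline regression on baseline and a mixed model with a shared baseline mean are nearly the same. On the binary scale they are not. For the 0.45 SD shift, the log-odds ratio is about −0.75, −0.81 and −0.95 at rho 0.3, 0.5 and 0.7 for endline adjusted for baseline status, against −0.90, −1.08 and −1.43 for a random-intercept logistic model. This stands, so one model has to be named.

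**Conclusion.** The point holds as one of precision. For A-versus-B OHRQoL, the planned terms give a difference in change, and the free baseline group term removes no bias because baseline is measured before randomisation. A baseline-adjusted analysis is generally more precise.

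Under the stated assumptions the loss for the median-split outcome is roughly 10 to 21 points of power (91 − 81 to 83 − 62). For a continuous score with equal SDs, an effect detected with 80% power would be detected with 94%, 90% or 86%. The gain shrinks as the endline SD rises above the baseline SD, to about 0 to 8 points at a ratio of 1.3, and it is small where power is already high.

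A reader might infer that chance imbalance makes the planned estimate biased, exaggerating or hiding the effect. It does not. The estimator is unbiased over randomisation, chance imbalance is already in its standard error, and type I error is about 5%. Nor does the criticism extend to B versus C: those groups are not randomised, so a shared baseline cannot be assumed. Preterm birth, its analysis and its sample size are untouched.

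**What to change.** For A versus B only, replace the OHRQoL model in Statistical analyses with one named model: regression of endline OHIP-14 on group with baseline OHIP-14 as a covariate, logistic if the median split is kept. State that the group coefficient is the treatment effect. In the logistic form, say that it is an odds ratio conditional on baseline.

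A mixed model on both time points without the group main effect may be kept as a sensitivity analysis. If the outcome is binary, note that its odds ratio is a different quantity, so the two estimates should not be expected to agree.

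Keep the group main effect in the B-versus-C model.

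The cost is a sentence or two of analysis wording. It needs no new data and no extra participants. Data collection is expected to run to September 2026 (Trial status), so the change can be made and dated before analysis.
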